## Abstract

**Background:**

Obesity in pregnancy increases the risk of gestational diabetes mellitus (GDM) and associated adverse outcomes. Despite metabolic differences, all pregnant women with obesity are considered to have the same risk of developing GDM. Improved risk stratification is required to enable targeted intervention in women with obesity who would benefit the most. The aim of this study is to identify pregnant women with obesity at higher risk of developing GDM and, in a pilot randomised controlled trial (RCT), test feasibility and assess the efficacy of a lifestyle intervention and/or metformin to improve glycaemic control.

**Methods:**

Women aged 18 years or older with a singleton pregnancy and body mass index (BMI) ≥ 30kg/m^2^ will be recruited from one maternity unit in London, UK. The risk of GDM will be assessed using a multivariable GDM prediction model combining maternal age, mid-arm circumference, systolic blood pressure, glucose, triglycerides and HbA1c. Women identified at a higher risk of developing GDM will be randomly allocated to one of two intervention groups (lifestyle advice with or without metformin) or standard antenatal care. The primary feasibility outcomes are study recruitment, retention rate and intervention adherence and to collect information needed for the sample size calculation for the definitive trial. A process evaluation will assess the acceptability of study processes and procedures to women. Secondary patient-centred outcomes include a reduction in mean glucose/24h of 0.5mmol/l as assessed by continuous glucose monitoring and changes in a targeted maternal metabolome, dietary intake and physical activity. A sample of 60 high-risk women is required.

**Discussion:**

Early risk stratification of GDM in pregnant women with obesity and targeted intervention using lifestyle advice with or without metformin could improve glucose tolerance compared to standard antenatal care. The results from this feasibility study will inform a larger adequately powered RCT should the intervention show trends for potential effectiveness.

**Trial registration:**

This study has been approved by the NHS Research Ethics Committee (UK IRAS integrated research application system; reference 18/LO/1500). EudraCT number 2018-000003-16.

## Introduction

Global estimates suggest that over 21% of women will be obese by 2025 [1]. In the UK, over 20% of women present with obesity at their first antenatal visit [2]. Obesity adversely affects reproductive health [3]. Pregnant women with obesity have a higher risk of developing most pregnancy complications, including gestational diabetes mellitus (GDM) [4, 5] and women with GDM are more likely to develop hypertension and pre-eclampsia during pregnancy [6, 7] as well as cardiovascular disease and type 2 diabetes later in life [8–10]. Infants born to mothers with GDM are more likely to be born large-for-gestational age (LGA) and macrosomic, increasing the risk of complications at delivery, including shoulder dystocia [7, 11]. Furthermore, offspring of GDM mothers have a higher risk of being overweight or obese [12], developing diabetes [13, 14] or metabolic disease [15, 16] later in life.

UK guidelines recommend that all pregnant women with obesity undergo an oral glucose tolerance test (OGTT) at 24–28 weeks’ gestation to detect GDM and introduce treatment [17]. Evidence suggests, however, that excessive fetal growth precedes the time of diagnosis in obese women [18]. Furthermore, marked abnormalities in the metabolic profiles of obese women who develop GDM may occur at least 10 weeks before conventional diagnosis [19, 20].

Several randomised controlled trials (RCTs) have attempted to prevent adverse outcomes in obese women; diet and physical activity [21] or pharmacological interventions [22–24] have overall not been effective. This has shifted the focus to targeted intervention for those individuals identified at greatest risk and increasing evidence suggests that this approach might be beneficial. The RADIEL RCT of a lifestyle intervention in 293 Finnish pregnant women, of whom 30% had previous GDM, demonstrated a reduction in GDM from 21.6 to 13.9% [25]. This observation was further supported by a UK multicentre randomised trial (ESTEEM) of a Mediterranean-style diet in women with risk factors including obesity, chronic hypertension or hypertriglyceridaemia, in which a reduction in GDM of 35% in the intervention group was achieved [26].

Although several studies describe tools developed to predict GDM in weight heterogenous women [27–33], specific approaches for pregnant women with obesity are rare. At present, all pregnant women with a body mass index (BMI) ≥ 30 kg/m^2^ are considered at high risk of developing GDM, although the majority do not develop the condition [34]. Our prediction tool for GDM was constructed using a range of biochemical and clinical factors in early pregnancy obtained in a cohort of 1303 obese pregnant women who took part in the UK Pregnancies Better Eating and Activity Trial (UPBEAT) [34]. The tool was developed using the clinical variables maternal age, blood pressure and mid-arm circumference and the biomarkers HbA1c, glucose and triglycerides. At a threshold of ≥ 35% risk, the tool identifies in early pregnancy obese pregnant women with a higher risk of developing GDM (1 in 2 chance) when diagnosed using The International Association of Diabetes and Pregnancy Study Groups (IADPSG) criteria and thereby those who might benefit most from an intervention [35].

In this, the next step, a pilot study will be undertaken in which pregnant women with obesity and at higher risk of developing GDM as identified using the prediction tool will be randomised to one of two interventions designed to improve glucose tolerance or to standard antenatal care.

### Study objectives

The objectives of the UK Pregnancies Better Eating and Activity Trial-Taking It Forward (UPBEAT-TIF) study are:*Primary feasibility outcomes*: To evaluate the feasibility (recruitment, retention, intervention adherence, determination of sample size) and acceptability of the UPBEAT-TIF intervention in women who are identified as having a higher risk of developing GDM*Secondary patient-centred objectives*To assess in pregnant women with obesity, identified as high risk for GDM, the efficacy of (a) lifestyle advice (diet and physical activity) and (b) metformin treatment plus lifestyle advice, to improve maternal glycaemic control, when compared with (c) standard careTo determine the impact of each intervention on a targeted maternal metabolomeTo examine the effect of each intervention on dietary intake and physical activity

## Methods and analysis

This protocol paper is written in accordance with the Standard Protocol Items: Recommendations for Interventional Trials (SPIRIT) checklist [36].

This study will be a single-centre, open-label, randomised controlled trial. NHS Research Ethics Committee approval has been obtained (UK IRAS integrated research application system; reference 18/LO/1500). Women will be recruited in one centre, from the antenatal clinics of Guy’s and St Thomas’ NHS Foundation Trust, London, UK (Fig. 1). Pregnant women with obesity will be invited to be screened for risk of developing GDM at their routine nuchal ultrasound scan appointment at St Thomas’ Hospital. Women will be eligible to take part in the study if they meet the following criteria:Over 18 yearsBMI ≥ 30kg/m^2^Higher risk of GDM as identified by risk assessment at screeningSingleton pregnancyGestation 11–14^+6^ weeks’ at the time of screeningWilling and able to give written informed consent

**Fig. 1 Fig1:**
[figure not shown]
CONSORT study flow diagram for the UPBEAT-TIF study

Women will be excluded if they meet the following criteria:Women identified as being at background risk of GDM at screeningTaking metformin or any medications that affect insulin sensitivityHbA1c ≥6.5% at the time of screeningPre-existing medical conditions including diabetes, thyroid disease, coeliac disease, hypertension, sickle cell, systemic lupus erythematosus, antiphospholipid syndrome, thalassaemia and current psychosisPast bariatric surgeryMultiple pregnancyInsufficient understanding of the trialContraindications to metforminParticipation in another investigational medicinal product trial at the time of screening

### Study entry

#### 11–14^+6^ weeks’ gestation appointment: screening

Eligible women will be contacted by a clinical research practitioner/assistant and offered information about the study before their routine nuchal ultrasound scan appointment in the antenatal clinic of St Thomas’ Hospital. Eligible women will also be approached in the antenatal clinic, given information about the study and offered the prediction test to identify the risk of later GDM development. Following informed written consent, weight will be measured and a blood sample taken at the same time as routine blood sampling for measurement of HbA1c, glucose and triglycerides. Clinical risk factors will also be recorded (age, blood pressure, mid-arm circumference) for risk assessment. Risk will be assessed by the algorithm previously described [35].

All women screened will be contacted by telephone. Women identified as being at background risk of developing GDM will be managed according to clinical guidelines and will not enter the trial. Women identified as being at a higher risk will be invited to be randomised into an antenatal programme of lifestyle advice, lifestyle advice plus metformin treatment or standard antenatal care.

#### 13–15^+6^ weeks’ gestation appointment: baseline and randomisation

At the first appointment, informed consent will be obtained by the chief investigator from women to be randomised into the trial. All participants will be fitted with a glucose sensor (Dexcom G6) to be worn for 7–10 days. The sensors are small, easy to wear, waterproof devices which require no finger prick calibration. The sensors will be applied to the back of the upper arm or abdomen of the participant and activated in blinded mode. To assess dietary intake, a semi-quantitative food frequency questionnaire (FFQ) will be administered to evaluate dietary glycaemic load (GL), glycaemic index (GI), saturated fat and other dietary variables [34]. Physical activity will be assessed by Axivity accelerometer AX3 (https://axivity.com/product/ax3).

Following the baseline assessment, randomisation will be performed electronically by the research team via a secure online-based data management platform (MedSciNet™) in order to conceal the sequence until interventions are assigned. Women will be randomised (1:1:1) into three groups:

a. Lifestyle advice

b. Lifestyle advice plus metformin

c. Standard antenatal care

The randomisation schedule will be minimised according to ethnicity (Black, White, Asian, Other), BMI (30−34.9kg/m^2^, 35−39.9kg/m^2^, ≥40kg/m^2^), parity (nulliparous/multiparous) and age. Participants will be allocated sequential study numbers regardless of allocation to the intervention or standard care group. Due to the nature of the study design, it will not be possible to blind participants or research staff to the randomisation arm.

#### Intervention

##### Lifestyle advice

Participants allocated to the lifestyle advice or lifestyle advice plus metformin arms will receive the intervention. The dietary intervention, delivered by a nutritionist, focuses on reducing GL and saturated fat intake using a regime previously shown to be effective in changing diet in ‘all risk’ obese pregnant women [34]. The dietary component of the intervention will aim to promote a healthier pattern of eating without restricting energy intake. The dietary advice will be tailored according to the woman’s habitual diet and cultural preference.

To decrease GL, participants will be encouraged to exchange starchy foods with a medium to high GI for those with a lower GI and reduce the consumption of sugar-sweetened beverages including fruit juice. Specific dietary goals will be provided for each participant that focus on differentiating between carbohydrate-rich foods. This advice will include replacing high GI breads with lower GI breads such as granary/wholegrain/multigrain bread, sourdough and rye; replacing high GI breakfast cereals with lower GI varieties such as porridge, oat-based cereals and no-added-sugar muesli; and encouraging consumption of lower GI grains like basmati rice, pearl barley, cracked wheat (bulgur), quinoa and pasta. To reduce saturated fat intake, participants will be encouraged to swap oils and spreads high in saturated fats (butter, lard, ghee) for those high in mono- and polyunsaturated fats (olive, sunflower); swap meat high in saturated fat (fatty meats, processed meat and meat products) for lean red meat, chicken and fish; and swap higher fat dairy foods (milk, cheese, yogurt) for lower fat varieties.

The physical activity component of the intervention will focus on a safe physical activity regime using the UPBEAT strategy which was shown to be successful in improving physical activity in ‘all risk’ pregnant women with obesity [34]. The advice aims to increase incremental walking and daily step count at a moderate intensity, being more active in daily life and reducing sedentary behaviour (sitting and screen time).

##### Metformin

In participants randomised to the lifestyle intervention plus metformin arm, metformin treatment will be initiated (500mg daily with food) and increased by 500mg every 2 to 3 days to achieve 2000mg within 2 weeks, taken as divided doses. Should side-effects occur, participants will be advised to reduce the current dose to that of the previous week and wait for 1 week before increasing the dose again. Treatment will be initiated after randomisation and continued until the delivery of the baby. Metformin will be dispensed at study visits and adherence assessed by tablet count.

Participants randomised to the lifestyle intervention arms will receive weekly sessions for 8 consecutive weeks. The sessions will be covered by video, email or telephone. Following a general review of the lifestyle or lifestyle plus metformin intervention, each session will be designed to deliver a different element of the intervention. The development of the UPBEAT lifestyle intervention was informed by psychological models of health behaviour, including control and social cognitive theory [34]. Participants will be encouraged to set achievable goals using the SMART (Specific, Measurable, Achievable, Relevant, Time Specific) goal approach, which will be reviewed on a weekly basis. In addition, participants will be asked to self-monitor their progress using a logbook. The participants will also receive a handbook with guidance on making the changes, along with recipe ideas and general information on eating while pregnant.

##### Standard care

Women randomised to the standard care group will attend all study visits except the 8 weekly intervention sessions and receive routine antenatal care according to local health care provision.

#### 22–25 weeks’ gestation appointment

All participants will be fitted with a continuous glucose monitoring (CGM) sensor for 7–10 days, again in blinded mode. Dietary intake and physical activity will be assessed using the FFQ and accelerometer. In the ‘lifestyle plus metformin’ arm, metformin will be dispensed, information on any side effects or adverse events will be collected and adherence will be assessed by tablet count.

#### 24–28 weeks’ gestation appointment

All participants will be asked to attend at 24–28 weeks’ gestation for an oral glucose tolerance test (fasting for a minimum of 10 h, 75 g glucose load). Routine clinical blood samples will be taken fasted and 2 h after the glucose load in accordance with The National Institute of Clinical Excellence (NICE) guidelines for the diagnosis of GDM [17]. Research blood samples will be obtained in the fasted state, 1 h and 2 h following the glucose load. For the purposes of the research, GDM will be diagnosed in accordance with IADPSG criteria: fasting capillary glucose ≥5.1mmol/L and/or 1-h glucose ≥10mmol/L and/or 2-h glucose ≥8.5mmol/L [37]. If a participant develops GDM (by NICE) during the study, she will be asked to continue with the medication and will be referred to the antenatal diabetes team for further advice and treatment. Weight will be measured at this visit.

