#### Secondary patient-centred outcomes

A reduction in mean glucose/24h of 0.5 mmol/L after 8 weeks of treatment compared to the standard arm as assessed using CGM.Other glycaemic parameters after 8 weeks of treatment; mean daytime glucose 0.700–23.00h, mean nocturnal glucose 23.00–0.700h, percentage time in tight glucose control target 3.5–6.7mmol/L, percentage time in recommended glucose control target 3.5–7.8mmol/L, area under the curve (AUC) <6.7mmol/L, AUC <7.8mmol/L, glucose variability measures (standard deviation (SD), coefficient of variation (CV)), high blood glucose index (HBGI) and low blood glucose index (LBGI).GDM diagnosis at 24–28 weeks (in accordance with IADPSG and NICE criteria).Metabolome; a targeted high-throughput nuclear magnetic resonance (NMR) metabolomic platform (http://computationalmedicine.fi/) will be used to measure metabolites from blood samples at baseline and at the time of the diagnostic OGTT. The platform quantifies lipid measures including lipoprotein particles (VLDL subdivided into 6 subclasses, IDL, LDL subdivided into 3 subclasses and HDL subdivided into 4 subclasses), constituents within each lipoprotein particle type (triglycerides, total cholesterol, free cholesterol and cholesterol ester levels and phospholipid concentrations), fatty acids, amino acids, glycolysis related metabolites, ketone bodies and inflammatory markers.Dietary intake and physical activity, including changes in GI, GL, saturated fat, time spent in light and moderate exercise and sedentary behaviour from baseline and after the 8-week intervention.

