### Sample size calculation and loss to follow-up

The study is intended as a pilot, one of whose aims is to gather the information needed for planning the definitive trial. This includes estimating the SD of the main outcome (the difference in mean 24-h glucose between arms) and checking the distribution. With twenty participants per arm, the SD can be estimated to within 80% of the true value. A 0.5mmol/L difference in mean 24-h glucose was considered to be of biological relevance based on data from comparable studies of CGM in pregnant women with obesity [39–41]. To account for up to 25% loss to follow-up and achieve a total sample size of 60, a sample of 84 women will be recruited.

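### The research GDM outcome rests its fasting limb on a capillary glucose and names no specimen for the other two limbs, although fasting, 1-h and 2-h blood is already drawn at that visit

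*Protocol article*

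**What the plan says.** All the relevant text on sampling is in the protocol article, section on the 24–28 weeks' gestation appointment, which describes three things for the same visit.

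- Routine sampling under NICE: "Routine clinical blood samples will be taken fasted and 2 h after the glucose load".
- Research sampling: "Research blood samples will be obtained in the fasted state, 1 h and 2 h following the glucose load".
- The research definition: "GDM will be diagnosed in accordance with IADPSG criteria: fasting capillary glucose ≥5.1mmol/L and/or 1-h glucose ≥10mmol/L and/or 2-h glucose ≥8.5mmol/L".

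The word capillary is attached to the fasting value alone. No specimen is given for the 1-h and 2-h values, and the article schedules no capillary test anywhere else. It does not say whether the research samples are venous or whether they are assayed for glucose.

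The Secondary patient-centred outcomes section lists "GDM diagnosis at 24–28 weeks (in accordance with IADPSG and NICE criteria"). The Introduction describes the women selected by the prediction tool as having a "higher risk of developing GDM (1 in 2 chance) when diagnosed using The International Association of Diabetes and Pregnancy Study Groups (IADPSG) criteria". It does not say which specimen was used in the cohort behind that figure.

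**The concern.** A diagnosis made by comparing a number with a fixed cut-off depends on how the number is measured. Here one limb of a three-limb rule is tied to a named specimen, and that specimen is not obviously any of the samples the same section schedules. Two readings are possible. If capillary is intended, the fasting limb may come from a different measurement than the 1-h and 2-h limbs, and from a different fasting value than the one used for the NICE diagnosis of the same woman at the same visit. If it is a slip for the fasting research sample, staff who follow the text could still assign the outcome from the wrong measurement. In both cases the sentence needs to change.

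What is at stake is the proportion with GDM by IADPSG criteria. The Discussion says that the next trial would be powered for a reduction in the prevalence of GDM, so the pilot's proportion is a natural planning input. Extra noise or a shift in one limb would move or blur it. NICE-criteria GDM is reported as well, but that does not repair the IADPSG outcome.

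**Working it through.** **The plan's own figure.** There is none to reproduce. The article gives no fasting glucose distribution, capillary error, capillary bias or misclassification rate. What follows is an illustration, and every input to it is an assumption.

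**Inputs.** From the article: cut-off 5.1 mmol/L; planned total of 60 women, used only for scaling. Assumed: laboratory fasting glucose V normal with mean 4.8 to 5.1 and SD 0.4 to 0.5 mmol/L; capillary CV 3 to 7%; bias b of 0, +0.2 or −0.2 mmol/L.

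**Model.** Capillary reading C = V × (1 + e) + b, with e normal, mean 0 and SD equal to the CV. Discordance on the fasting limb is D = P[(V ≥ 5.1) differs from (C ≥ 5.1)]. Taking V as the reference is part of the assumption: the article does not say which specimen the cut-off refers to, so D measures disagreement between two ways of measuring, not proven error.

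**Step 1: range of D on the fasting limb.**

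| Bias (mmol/L) | Lowest D | Highest D |
|---|---|---|
| 0 | 7.9% (mean 4.8, SD 0.5, CV 3%) | 23.2% (mean 5.1, SD 0.4, CV 7%) |
| ±0.2 | 11.5% (mean 4.8, SD 0.5, CV 3%, b = −0.2) | 26.7% (mean 4.9, SD 0.4, CV 7%, b = +0.2) |

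Overall this is about 8 to 27%. In 60 women: 0.079 × 60 ≈ 5 to 0.267 × 60 ≈ 16.

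**Step 2: one central setting** (mean 4.9, SD 0.5, CV 5%). The fasting-positive proportion on laboratory values is P(Z ≥ (5.1 − 4.9)/0.5) = P(Z ≥ 0.4) = 34%.

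| Bias (mmol/L) | D | Fasting-positive by capillary |
|---|---|---|
| 0 | 13.9% | 35% |
| +0.2 | 19.2% | 49% |
| −0.2 | 15.6% | 23% |

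Noise alone reclassifies women in both directions and barely moves the proportion. A bias of 0.2 mmol/L moves it by 11 to 15 percentage points.

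**Step 3: the three-limb composite.** A woman positive at 1 h or 2 h keeps her diagnosis whatever the fasting value. If a share q is positive on those limbs independently of the fasting limb, composite discordance is D × (1 − q). With an assumed q of 25%: 0.75 × 7.9% ≈ 6% to 0.75 × 26.7% ≈ 20%, or about 4 to 12 of 60. In practice the limbs are likely to be correlated, so this is a rough guide.

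**Step 4: effect on the between-arm comparison.** Assume an intervention lowers mean fasting glucose by 0.1 mmol/L, from 4.9 to 4.8, with SD 0.5.

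| Reading | Control | Intervention | Risk ratio | Difference |
|---|---|---|---|---|
| Laboratory | 34.5% | 27.4% | 0.80 | 7.0 points |
| Pure shift −0.2 | 21.2% | 15.9% | 0.75 | 5.3 points |
| Pure shift +0.2 | 50.0% | 42.1% | 0.84 | 7.9 points |
| Noise only, CV 5% | 35.4% | 29.0% | 0.82 | 6.4 points |

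Random noise pulls the risk ratio towards 1. A shift can move the ratio or the difference either way.

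**The case against.** The strongest case against is that this is a wording slip in a condensed article. Fasting blood is drawn twice over at the visit and no capillary test is scheduled elsewhere, so the word may have no practical effect, and assay detail often sits in the full protocol. Part of this stands: the text cannot settle whether the word is intended. But the article does not merely leave the specimen out; it fixes one, for one limb only, and the sampling described beside it does not match.

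The limited impact also stands. GDM is one of several secondary outcomes in a pilot, and the same rule applies to every arm. The sample-size information the pilot is set up to deliver is the SD of mean 24-h glucose. With 20 women per arm and a risk of 50%, the 95% interval for one arm is about ±1.96 × √(0.5 × 0.5/20) = ±22 percentage points, wider than the shift of 11 to 15 points in the central setting.

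Four stronger inferences are tempting, and the article supports none of them:

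- *Many women sit close to 5.1 mmol/L.* No glucose distribution is reported.
- *Any between-arm difference is diluted.* Noise does this in general; step 4 shows that a shift need not.
- *Comparison with the 1 in 2 risk is broken.* The specimen used in the prediction-tool cohort is not stated. If it was capillary, a laboratory value here would itself introduce the difference.
- *Open-label staff would selectively repeat bedside readings.* Neither a bedside meter nor repeat testing is mentioned.

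**Conclusion.** The point holds as a badly fixed outcome definition. The fasting limb is tied to a capillary specimen, the other two limbs to none, and suitable time points for a uniform definition are already in the schedule. The consequence is conditional: the GDM proportion *could* change. Under the assumed inputs about 8 to 27% of women change category on the fasting limb, and about 6 to 20% on the composite if an independent 25% are positive on the other limbs. Neither range comes from the article, and other plausible inputs widen them: with means of 4.7 or 5.0, a CV of 2 to 7.5% and a bias of 0 to +0.3 mmol/L, the fasting-limb figure runs from 5 to 31%.

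A reader might infer that women will be misclassified in a known number. That would require knowing which specimen the cut-off refers to, how the capillary reading behaves and how fasting glucose is distributed, and the article gives none of these. The impact on this pilot is modest, but the correction is cheap enough to be worth making.

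**What to change.** For the research outcome only, delete the word capillary and state that all three limbs (fasting, 1 h and 2 h) are judged on laboratory glucose from the blood samples already scheduled at the 24–28 week visit, with one specimen type and one assay for all time points and all arms. The clinical diagnosis under NICE and the referral that follows from it are not touched.

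The cost is a one-sentence amendment with no added visit. Because the article does not say that the research samples are assayed for glucose, the sponsor must confirm that the sample type is suitable and that the laboratory assay will be run on them. If the prediction-tool cohort used capillary fasting values, that difference should be reported when the observed GDM proportion is set beside the 1 in 2 risk.
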